### ACT description

#### ACTFAST context

The current study describes one part of our larger effort to implement the Anesthesiology Control Tower (ACT), a novel, telemedicine-based intervention for the operating suite. The purpose of the research described in the current protocol is to use iterative usability testing over the course of approximately 6 months, in order to create a maximally useful and usable resource for our clinicians. A second, concurrent study by our group (Anesthesiology Control Tower: Forecasting Algorithms to Support Treatments, or ACTFAST2) is working to develop, refine, and validate forecasting algorithms to predict negative patient trajectories; such algorithms will serve to help inform ACT interventions. Our final phase of investigation will be a yearlong comparative effectiveness randomized controlled trial (Anesthesiology Control Tower: Feedback Alerts to Supplement Treatments, or ACTFAST3; NCT02830126) to demonstrate the utility of the ACT in improving adherence to clinically relevant practice guidelines and to evaluate the effect of the ACT on surrogate measures of patient outcome. In this trial, each of our institution’s adult ORs will be randomized on a daily basis either to a control group or to an experimental group in which anesthesia providers in those ORs will receive the support of the ACT. This support will be communicated in the form of additional alerts sent by the physicians in the ACT, whose responsibility is to filter and prioritize information, thus maximizing alert quality and minimizing false alarms.

#### ACT technology

One of the key components of the ACT technological infrastructure is an advanced clinical monitoring and display system called AlertWatch ® (Ann Arbor, MI). AlertWatch (AW) uses a multi-threaded Java-based server to collect and integrate clinical information from multiple distinct data sources for presentation in a simplified and intuitive manner (see Figs. 1, 2 and 3). AW provides alerts based on its continual analysis of the current patient state; when patient parameters fall outside of predetermined set points, AW triggers written and auditory alarms within the patient display and on the census view. The AW Tower Mode platform used in this study is distinct from the commercially available product in many ways and will be refined based on the results of the present study.

AlertWatch and all additional electronic records used by our hospital are available via secure Internet connection to clinicians at any physical location in the world, allowing for the creation of our remote ACT. This includes our anesthesia information management system, MetaVision (iMDsoft®, Needham, MA; Centricity, General Electric Healthcare), which contains both manually entered data and automatically recorded physiologic data for the perioperative period.

#### ACT structure

The ACT is physically housed within the hospital complex and is remoted from the physical operating rooms. This room includes three computers: two with two monitors and one with three monitors (one being a flat panel TV screen). An additional flat panel TV screen is powered by the third computer. The presence of additional monitors allows multiple AW windows to be visible, in addition to providing space for the separate, necessary software programs that will be needed. All software (i.e., our electronic medical record, our anesthesia information management system, and AW) either is accessible on these computers through desktop icons or links through our department’s webpage. A guide to the ACT and an AW help guide are provided in a physical format in addition to electronic copies. Two landline telephones and one iPhone will be available in the randomized control trial.

The ACT will be staffed by attending anesthesiologists and anesthesiology residents who are in their final year of training. The main role of these trained clinicians (referred to as “ACTors”) is to monitor all active ORs by making use of AlertWatch, the hospital’s EMR, and the anesthesiology information management system. ACTors will assess and address alerts within the AW Tower Mode platform (Figure 3) and will use their clinical judgment to determine whether a particular alert warrants contact with the clinicians in the OR (CORs) to provide additional support.

## Appendix 2

### Debriefing scripts

#### Debriefing script for phase Ia (ACTor sessions)

*Thank you for filling out the questionnaires. Before you leave, I would love to talk briefly about your overall impression of the ACT.*

*Right now how do you feel about the ACT after the session today?*

*Were there problems that you encountered with any of the software?*

*Were there problems that you encountered with the physical set up?*

*Was there anything in the AlertWatch program or the other software that you think worked well?*

*Was there anything in the physical set up of the ACT that you think worked well?*

#### Debriefing script for phase Ib (COR sessions)

For each case scenario:

*What thoughts come to your mind as you imagine this [scenario]?*

*Would you want to communicate with the ACT? If so, what would you communicate?*

*Do you think the ACT would be helpful in this situation?*

*If yes, what makes it helpful?*

*If not, what keeps it from being helpful?*

*Could it ever be helpful?*

For the final debriefing:

*Now that we are finished with that part [of the session], do you have additional general thoughts about the ACT?*

*What are instances in which you think it would be beneficial to receive an alert or assistance from the ACT?*

If participant cannot think of instances, prompt further: *is there any clinical situation that you can think of in which it would be helpful to receive alerts from the ACT?*

*What are instances in which it would be*

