#### Data analysis

Given that the “think-aloud” and similar methods often slow task completion and thought processes [21], the focus of analysis will be on qualitative usability data via content analysis, although a few relevant quantitative measures will be included. Participant demographics will be reported with descriptive statistics. Mean scores from the SUS, the NASA-TXL, and the overall CSUQ score and subscale scores will be calculated and reported in addition to 95% confidence intervals. Quantitative data from phase Ia will include time to task completion and rate of task completion.

Audio recordings from each participant in both phase Ia and phase Ib will be professionally transcribed. The investigators will review the transcripts to identify themes and create a codebook with themes and subthemes surrounding the usability of the ACT [32]. We will use a qualitative data analysis software program (NVivo®) to organize and code the transcripts. We will perform a content analysis of key themes based on the frequency and level of emotive force expressed by participants. Themes will be examined within and across user groups (physician anesthesiologists, CRNAs). Research team members trained in qualitative methods will perform the coding independently until inter-rater reliability is reached. Minor discrepancies will be resolved through discussion and consensus. If there are major discrepancies, we will refine the codebook and recode.

Decisions to modify components of the pilot ACT during the usability testing will be determined by the investigative team, based on participant feedback, and will occur in an iterative fashion.

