***not***
*be beneficial or helpful to receive an alert?*

*What form of alert, phone call, text, or page, would be most helpful? Would that ever change?*

*Do you have any other feedback, concerns, or questions before we end?*

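### The Phase Ib script re-probes only towards helpful uses of the ACT, so positive themes may be modestly inflated and barriers under-elicited

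*Protocol article*

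**What the plan says.** Appendix 2 of the protocol article prints the Phase Ib script for clinicians in the operating room (CORs).

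- **Per scenario.** After an open question on the participant's thoughts, one on communicating with the ACT, and one on whether the ACT would help, the script branches: "If yes, what makes it helpful" and "If not, what keeps it from being helpful". Next comes "Could it ever be helpful".
- **Final debriefing.** The positive question is "What are instances in which you think it would be beneficial to receive an alert or assistance from the ACT". It is followed by the instruction "If participant cannot think of instances, prompt further", with a reworded request for any helpful clinical situation. The negative question asks for instances in which it would not "be beneficial or helpful to receive an alert". No second prompt follows it. The script closes by inviting further feedback, concerns or questions.

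The Phase I Data analysis section states how the transcripts are used: "We will perform a content analysis of key themes based on the frequency and level of emotive force expressed by participants". It also says that the investigative team will modify the ACT on the basis of participant feedback.

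**The concern.** A second probe gives a participant another chance to produce a mention. If that chance is offered on one side only, mentions on that side can rise without any difference in underlying opinion. Both extra probes here aim at helpful uses. They fall on participants who have just seen no use for the ACT in a scenario, or who could name no instance in which an alert would help. A participant who said the ACT would help is not asked in that scenario when it might get in the way. One who draws a blank on the negative question is not asked again.

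This matters because of what Phase Ib is for. The article chooses the think-aloud approach partly for its ability to reveal barriers to adoption. Phase Ib is the only stage of this study that puts clinicians in the recipient role, and the only one that includes nurse anesthetists (Table 1). Phase II participants do not interact with CORs. The three rating scales are specified for Phases Ia and II, and none is described for Ib. Within this study the interview therefore carries the recipients' evidence.

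**Working it through.** The article gives no figure on this point to reproduce, so the check is a count of script items by direction and type, set against the analysis rule.

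| Item type in the Phase Ib script | Towards helpful | Towards unhelpful |
|---|---|---|
| Main question or branch | 2 (the yes branch; beneficial instances) | 2 (the no branch; non-beneficial instances) |
| Second probe | 2 (could it ever help; conditional second prompt) | 0 |
| Scope of the final question | alerts and assistance | alerts only |

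Three further items are open and take no side: thoughts on the scenario, general thoughts, and closing feedback or concerns. No item names harm or interference.

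**Step 1: is the asymmetry real?** Yes, at the level of second probes (2 against 0) and in the scope of the final question. At the level of main questions and branches the script is balanced (2 against 2).

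**Step 2: who receives the extra probes?** The scenario probe is printed directly after the no branch, and its wording fits someone who has just answered no. The final prompt is explicitly conditional on naming no helpful instance. Those who answer no are first asked for their reasons, so their barriers are collected. The barriers more likely to be missed are those held by participants who answer yes, and by those who need a second prompt on the negative question.

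**Step 3: does it reach the analysis?** Frequency is one of two stated inputs to the content analysis, the other being emotive force. Additional helpful mentions obtained by re-prompting can therefore enter the frequency input.

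**Step 4: how large could it be?** A calculation would need the number of scenarios, the share of participants answering no, the share naming no instance unprompted, and the yield of each second probe. The article gives only the sample size, 10–15 participants. The effect cannot be computed. The expected direction is towards more helpful mentions, although a probe could also draw a firm refusal.

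**Step 5: what does the same appendix do elsewhere?** The Phase Ia script asks two questions about problems and two about what worked well, problems first, with no one-sided second probe. The Phase Ib script is thus less even-handed than its companion.

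**The case against.** The case on the other side has real weight.

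- **Negative views are sought.** There is a matched no branch and a matched final question, and concerns are invited at the end. According to the Phase Ib procedure, open initial reactions come before the scenarios, and free think-aloud comes before the scripted questions in each. This stands, and it dilutes the asymmetry. It does not remove it, because re-prompted mentions are added to the spontaneous ones.
- **The extra probes serve a formative purpose.** Asking a sceptic whether the ACT could ever help may show what would have to change. This stands as a reason to keep the probes. It is no reason to leave them without a mirror.
- **The analysis estimates no proportion of supporters.** This stands. A reader might infer that themes are ranked by frequency and that the results are therefore biased towards endorsing the ACT. The article does not say so: it combines frequency with emotive force and plans no count of helpful against unhelpful mentions.
- **Alert selection does not hang on these counts.** A reader might also infer that it does. The Phase II Data analysis section judges the usefulness of individual alerts from how often Phase II users rate them significant or insignificant. That stands. Phase Ib feedback does still inform changes to the ACT, and the Phase Ib procedure says the scripted questions seek views on the usefulness of particular alerts.
- **Recipients will be heard again.** The Discussion anticipates surveys of the anesthesia department in the later trial. True, but those are described as post-implementation analyses, after the redesign that this study informs.
- **Coding rules may sit in a fuller document.** They may, so the absence of a rule for prompted mentions is not a fault here. The point rests on the printed script.

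**Conclusion.** The point holds in a limited form. The Phase Ib script is balanced in its main questions and branches, but it re-probes only towards helpful uses (2 against 0) and gives its final negative question a narrower scope. Since frequency is a stated input to the content analysis, positive themes may be modestly inflated and barriers under-elicited. That is a risk built into the instrument, not a demonstrated bias, and no size can be put on it from the document. The conclusion assumes that the script is used as printed and that some participants respond to a second probe with a mention they would not otherwise have made. It is a cheap improvement to make and does not threaten the study's conclusions.

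**What to change.** 1. After the yes branch in each scenario, add a mirror probe such as *Could it ever be unhelpful or get in the way?*
2. Add to the negative question in the final debriefing the same conditional second prompt that the positive question has.
3. Widen that negative question to cover assistance from the ACT as well as alerts, to match the positive one.
4. At coding, flag any mention that arises only after a second probe, and report theme frequencies with and without the flagged mentions. Do not discard scripted answers: most of the direct evidence on unhelpful uses is itself elicited by a question.

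The existing probes stay. The cost is one or two extra minutes in a session of about 30 minutes, plus one coding flag. The script changes have to be made before the interviews, because a probe that was not asked cannot be recovered from a transcript. The flag can be applied to transcripts at any time.

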***not***
*be beneficial or helpful to receive an alert?*

*What form of alert, phone call, text, or page, would be most helpful? Would that ever change?*

*Do you have any other feedback, concerns, or questions before we end?*

## Abbreviations

ACT: Anesthesiology Control Tower
ACTor: clinician in the Anesthesiology Control Tower
AW: AlertWatch
COR: Clinician in the operating room
CRNA: Certified registered nurse anesthetist
CSUQ: Computer System Usability Questionnaire
IT: Information technology
NASA-TLX: NASA Task Loading Index
OR: Operating room
SUS: System Usability Scale
